## 10 ASSESSMENT OF SAFETY

No treatments are administered as part of this survey and collection of any treatment-related effects, both safety and efficacy, are out of scope. There will be no specific safety data collection in this survey. However, Investigators must comply with all Adverse Event (as defined below), Other Safety Information (as defined below) and Product Complaint (as defined below) reporting obligations under applicable laws in Belgium.

Investigators must send copies of all reports (including but not limited to interim study reports, final study reports, etc.) submitted to any health authority or regulatory agency regarding an Alnylam product in parallel to Alnylam at: [contact] or [contact].

Investigators shall ensure that any personal information collected about individuals complies with applicable privacy and data protection laws and regulations.

In addition, after receiving the data collection form from physicians, the data will be screened by Modis to identify any potential adverse event (as described below) any Other Safety Information (as defined below) and any Product Complaint (as defined below), which will be reported to Alnylam PV department for further assessment within 24 hours. Alnylam PV department may contact the reporting physician to obtain further information needed to fulfill its reporting obligations.

**Definition of an Adverse Event (AE):** An AE means any untoward medical occurrence in a patient or Clinical Trial subject administered a Medicinal Product and which does not necessarily have to have a causal relationship with this treatment. An adverse event can therefore be any unfavorable and unintended sign (for example, an abnormal lab finding) symptom, or disease temporally associated with the use of a Medicinal Product, whether or not considered related to this Medicinal Product.

**Definition of Other Safety Information:** Other Safety Information means circumstances where a report does not include an AE per se, but nevertheless needs to be reported to Alnylam. These circumstances include:

- Use of a product during pregnancy or breastfeeding
- Overdose
- Abuse
- Misuse
- Medication error
- Occupational exposure
- Lack of therapeutic efficacy
- Off-label use
- Suspected transmission via a medicinal product of an infectious agent

- Suspected or confirmed counterfeit/falsified medicinal product

**Definition of Product Complaint (PC):** Any written, electronic, or oral communication that alleges deficiencies related to the identity, quality, durability, reliability, safety, effectiveness, or performance of a medicinal product, medical device, or combination product after it is released for distribution. Product complaints are typically non-medical in nature; however, it is possible that complaints could be associated with an adverse event.

## 11 STATISTICAL ANALYSES

### 11.1 Endpoints

#### 11.1.1 PRIMARY ENDPOINTS

##### Total cohort:

Number of patients with hATTR

- Number of patients with hATTR by type of treatment

##### Onpattro Subcohort:

Onpattro® treatment use in terms of:

- Treatment start & stop dates (with reason for stopping)
- Prescribed dosage of Onpattro® (in mg/kg) at the beginning of each cycle
- Total number of Onpattro® vials consumed, at the end of each cycle
- Total number of Onpattro® treatment cycles
- Total number of Onpattro® vials at each timepoint (if available)

Onpattro® treatment compliance in terms of:

- Number of missed Onpattro® treatment cycles per year (if any)
- Treatment interruptions (if any), with dates of treatment discontinuation and treatment reinitiation (with reason for interrupting)

##### Neurological endpoints:

- FAP score (1, 2) as described by Coutinho (1980)
- EMG status (worsened, stable or improved)
- MRC S-S score (scale of 0-6)
- Functional independence measurements (FIM) score (scale of 1-7)

- NIS score (scale of 0-244)
- ACTIVLIM score (impossible, difficult, easy)
- CADT score (using a scale of 0-4; total normal score of 16 in women and 20 in men)
- VAS score for pain (using a visual analog scale)
- PND score (0, 1, 2, 3a, 3b, 4)

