The clinical manifestations of the length-dependent, symmetrical sensorimotor neuropathy are the result of amyloid-mediated injury to large and small peripheral nerve fibers. Sensory abnormalities include painful dysesthesias in the feet and hands, as well as loss of sensation leading to thermal burns involving the feet and hands and to joint injury in the lower limbs. Progressive muscle atrophy and motor weakness in both lower and upper limbs leads to impairment of ambulation and inability to perform other activities of daily living such as holding eating utensils or a drinking glass or managing buttons and zips. Autonomic dysfunction results in debilitating orthostatic hypotension, severe gastrointestinal symptoms (including early satiety, chronic nausea/vomiting, and both diarrhea and constipation), bladder dysfunction with dysuria and urinary retention, as well as cardiac arrhythmias [Connors, 2004; Plante-Bordeneuve, 2011; Ando, 2013]. Cardiac infiltration with amyloid leads to cardiomyopathy characterized by heart failure due to both diastolic and systolic dysfunction, conduction disturbances and arrhythmias [Connors, 2004; Benson, 2007; Plante-Bordeneuve, 2011; Ando, 2013; Swiecicki, 2015]. This constellation of progressive morbidity results in severe disability, wasting due to gastrointestinal malabsorption and malnutrition, and profound loss of quality of life. Death usually results from heart failure or infection, with a median survival of 4.7 years (range 1.3 to 24.8 years) following diagnosis [Plante-Bordeneuve, 2011; Swiecicki, 2015].

In terms of symptoms, four stages of hATTR with polyneuropathy (FAP stages) are distinguished. Patients with stage 0 disease are asymptomatic, patients with stage I (mild) disease are ambulatory, patients with stage II (moderate) disease are ambulatory but require assistance, and patients with stage III (severe) disease are bedridden or wheelchair-bound [Ando, 2013].

Since many of the systemic manifestations of the disease are caused by liver-derived circulating TTR, several treatment approaches aimed at reducing the amount of circulating amyloidogenic protein are currently used for hATTR: orthotopic liver transplantation (OLT), TTR tetramer stabilizers (including tafamidis) and gene silencing by ribonucleic acid interference [RNAi].

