## 8 PATIENT POPULATION

The population will consist of adult patients ( $\geq 18$  years old) with hATTR confirmed by genetic testing, with stage 1 or stage 2 polyneuropathy.

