## 8.2 Inclusion/exclusion criteria for patients

Inclusion criteria: adult patients ( $\geq 18$  years old) with a diagnosis of hATTR with polyneuropathy, confirmed by genetic testing.

Exclusion criteria: there are no specific exclusion criteria.

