**11.3 Planned analyses**

The analysis of the collected information will only consist of descriptive data such as frequencies, aggregated averages, standard deviations and ranges. No formal statistical analysis plan is set out, neither has there been any statistical hypothesis formulated. The final report of this survey will consist of a descriptive presentation of the collected data.

This is an observational survey and only data collected in routine clinical practice will be used. Only data available at the time of the survey are to be recorded, hence no substitution,

imputation, or other correction methods will be used to complete missing values. Statistical analyses will only be performed on parameters collected in sufficient numbers.

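### The FAP stage primary endpoint is defined with values 1 and 2 only, so progression from stage 2 to stage 3 (and improvement from stage 1 to 0) has no value on it

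*Protocol*

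**What the plan says.** The endpoint list in Protocol section 11.1.1 gives "FAP score (1, 2) as described by Coutinho (1980"), and the synopsis repeats the same entry. Section 5.1 states that "four stages of hATTR with polyneuropathy (FAP stages) are distinguished". At the lower end, "Patients with stage 0 disease are asymptomatic"; at the upper end, "patients with stage III (severe) disease are bedridden or wheelchair-bound".

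Table 1 (section 9.2) schedules polyneuropathy and FAP stage at all four timepoints: EAP initiation, first reimbursement, reimbursement prolongation and last evaluation. Its footnote points to the same 1980 reference and lists no permitted values. Section 6.1 makes clinical impact on neurological symptoms, from 01 July 2018 to 01 February 2021, a primary objective.

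The pair 1 and 2 matches the population described in section 8, adults "with stage 1 or stage 2 polyneuropathy". The formal criteria in section 8.2 set no stage limit and add that "there are no specific exclusion criteria".

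**The concern.** FAP stage is used here as a repeated outcome as well as an entry characteristic. The range that describes patients at entry appears to have been carried over to follow-up. In a disease that the Protocol itself calls progressive, a patient who starts at stage 2 then has no worse value to move to on this endpoint. The step that is lost is the one to being wheelchair-bound or bedridden.

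If the definition were applied literally, such a patient would be entered as 2, which reads as stable, or left without a value. Section 11.3 rules out completing missing data: no substitution, "imputation, or other correction methods will be used to complete missing values". The results go into a report to the Belgian health insurer on reimbursement, so a stage summary that cannot show this step could mislead the reader for whom it is written.

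**Working it through.** The Protocol gives no figure to reproduce. It is descriptive, with no hypothesis and no power calculation. The check is mainly a comparison of sections, followed by a short illustration of size.

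**1. Is (1, 2) a value set?** The reference list is unnumbered, so these are not citation numbers. The same list writes another scale with its levels in parentheses: "PND score (0, 1, 2, 3a, 3b, 4"). The natural reading is that 1 and 2 are the permitted values. The synopsis carries the same entry.

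**2. Which stages have a value?** The endpoint allows {1, 2}; section 5.1 recognises {0, I, II, III}. Two of four stages have none.

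| Stage at start | Later stage | Value available? |
|---|---|---|
| 1 | 0 (better) | No |
| 1 | 2 (worse) | Yes |
| 2 | 1 (better) | Yes |
| 2 | 2 (same) | Yes |
| 2 | 3 (worse) | No |

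**3. Does another section supply the missing values?** No. Table 1 and its footnote neither repeat the restriction nor lift it. Section 11.3 does not mention stage coding.

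**4. Weight of one patient.** Section 8.1 expects about 9-12 patients in the sub-cohort: 1/12 = 8.3% and 1/9 = 11.1%.

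**5. Chance that the gap matters.** Let k be the number of patients at stage 2 at Onpattro start and p the risk that each reaches stage 3 in the observation period. Both are assumptions, as the Protocol gives neither. The chance of at least one progression without a code is 1 − (1 − p)^k. With k = 5:

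- p = 0.05: 1 − 0.95^5 = 1 − 0.774 = 0.226, about 23%
- p = 0.10: 1 − 0.90^5 = 1 − 0.590 = 0.410, about 41%
- p = 0.20: 1 − 0.80^5 = 1 − 0.328 = 0.672, about 67%

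The figure rises with k and is zero if nobody starts at stage 2. A single p is a simplification. Patients treated from the EAP start could have about 31 months of exposure (July 2018 to February 2021), while those first treated at reimbursement on 01 December 2019 have at most 14.

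**The case against.** The strongest reply is that nothing shows an enforced cap. The data collection form is not among the documents, and Table 1 asks for FAP stage without listing values, so a site could write 3. Parentheses in the endpoint list are also loose elsewhere: CADT is given a 0-4 scale beside a normal total of 16 or 20, and the ACTIVLIM score is given as three answer words. This stands as a limit on the claim. The defect is in the endpoint definition; whether data would actually be lost is not known.

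Second, section 9.2 provides for completeness checks and queries to sites, so a blank would not simply disappear. That also stands, although a query cannot supply a value that the endpoint lacks.

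Third, a reader might infer that the FAP result is necessarily biased in favour of the drug. The documents do not support that. The truncation works at both ends, worsening from stage 1 to 2 stays visible, and the stage mix and transitions are unknown. Worsening can also appear on other primary endpoints: MRC S-S and FIM are scheduled at all four timepoints, NIS is scheduled at EAP initiation and collected later if available, and PND is collected if available.

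Fourth, a reader might apply the assumed risks to the whole sub-cohort of 9-12, which gives 37-46%, 61-72% and 87-93%. Those figures fit only if every patient starts at stage 2. A patient who went from stage 1 to 3 and was entered as 2 would still show as worsened.

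**Conclusion.** The point holds for the endpoint as defined. The synopsis and section 11.1.1 fix a value set that omits two of the four stages in section 5.1, for an outcome collected repeatedly over follow-up. From stage 2, only stability or improvement can be expressed. This is an error in what the Protocol states, and not a detail left for an analysis plan.

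Its size is conditional. Each affected patient is 8-11% of the sub-cohort. The 23%, 41% and 67% rest on an assumed 5 stage-2 patients with a common, independent risk of 5%, 10% or 20%. The finding itself does not depend on them. The documents do not establish that stage 3 would in fact go unrecorded, that the net bias favours the drug, or that the survey as a whole cannot see worsening.

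**What to change.** In the synopsis, section 11.1.1 and the data collection form, define the endpoint as FAP stage 0, 1, 2 or 3 at every timepoint. Keep stage 1-2 only as a description of the population at treatment start, and reconcile section 8, which names those stages, with section 8.2, which sets no stage limit. Report counts by stage at Onpattro start against stage at each later timepoint, with the number reaching stage 3 and the number missing shown explicitly.

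The cost is a one-line change made in two places, under the written amendment that section 12.2 requires, and at most two extra codes on the form. No new data are needed, because stage is already taken from the chart. The downside is that the reported result may look less favourable.

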**Cardiological endpoints:**

- Orthostatic hypotension (yes or no)
- NYHA score (class I-V)
- ECG status (worsened, stable or improved)
- Echocardiography status (worsened, stable or improved) + Cardiac Output percentage

**11.1.2 SECONDARY ENDPOINTS****Onpattro Subcohort: the following data will be collected if available****QoL endpoints**

- EQ5-D score
  - EQ5-D type
  - EQ5-D score
- SF-36 or SF-12 score (transformed to 0-100 scale; higher scores indicate better health-related QoL)

**11.2 Cohorts**

The total cohort will include all patients meeting the inclusion criteria (i.e. with a diagnosis of hATTR confirmed by genetic testing), for which aggregated data will be collected.

The Onpattro® sub-cohort will include patients with hATTR that have been treated with Onpattro® from the start of the Expanded Access Program (EAP) in 01 July 2018, up to 01 February 2021, for which individualized data will be collected.

**11.3 Planned analyses**

The analysis of the collected information will only consist of descriptive data such as frequencies, aggregated averages, standard deviations and ranges. No formal statistical analysis plan is set out, neither has there been any statistical hypothesis formulated. The final report of this survey will consist of a descriptive presentation of the collected data.

This is an observational survey and only data collected in routine clinical practice will be used. Only data available at the time of the survey are to be recorded, hence no substitution,

imputation, or other correction methods will be used to complete missing values. Statistical analyses will only be performed on parameters collected in sufficient numbers.

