APOLLO met its primary endpoint, modified NIS (mNIS)+7. An improvement in neuropathy compared to baseline (mNIS+7 change of <0 points) at 18 months was seen in 56.1% (95% confidence interval [CI]: 48.1%, 64.1%) of patients on Onpattro® compared to only 3.9% (95% CI: 0.0%, 8.2%) on placebo (odds ratio of 40.0,  $p=1.82 \times 10^{-15}$ ). The effect of Onpattro® on mNIS+7 was observed across all patient subgroups defined by age, sex, ethnicity, geographic region, TTR genotype, neuropathy severity, disease stage, prior TTR tetramer stabilizer use and cardiac subpopulation. APOLLO also met all of its secondary endpoints, including the key secondary endpoint of Norfolk QOL-DN [Adams, 2018].

Onpattro® received a marketing authorisation in the European Union on 27 August 2018 for the treatment of hATTR. An Expanded Access Program (EAP), was launched on 01 July 2018, to allow patients with hATTR to receive Onpattro®. Onpattro® received a temporary reimbursement from Belgian Health Insurance Agency (Rijksinstituut voor Ziekte- en Invaliditeitsverzekering / Institut national d'assurance maladie-invalidité [RIZIV / INAMI]) on 01 December 2019.

The recommended dose of Onpattro® is 300 µg/kg administered via intravenous infusion once every 3 weeks. Dosing is based on actual body weight. For patients weighing ≥100 kg, the recommended dose is 30 mg. Vitamin A supplementation at approximately 2500 IU vitamin A per day is advised for patients treated with Onpattro®.

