## 6 OBJECTIVES

### 6.1 Primary objective(s)

- To determine current hATTR patient numbers and clinical practice in terms of treatments used for all Belgian patients included in the total cohort, as on 01 Feb 2021.
- To determine the clinical impact of Onpattro® use in adult patients with hATTR, in real world circumstances, in the Onpattro® subcohort in terms of neurological and cardiac symptoms, for the period starting from 01 July 2018 (start of EAP), up to 01 February 2021.
- To establish real-world Onpattro® treatment use for adult hATTR patients treated with Onpattro® in the Onpattro® subcohort, for the period starting from 01 July 2018 (start of EAP), up to 01 February 2021.

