| Echocardiography                                   | X                                        | X                      | X                                          | X                                      |
| QoL parameters                                     |                                          |                        |                                            |                                        |
| EQ5-D                                  | X                                        | X                      | X                                          | X                                      |
| SF-36 or SF-12                         | X                                        | X                      | X                                          | X                                      |

 for patients that were included in the EAP

 or no longer treated/still on initial reimbursement

 up to 01 February 2021, if available

 For patients not included in the EAP

 if available

 as defined by Coutinho (1980)

**CADT** - Compound Autonomic Dysfunction Test; **ECG** - Electrocardiogram; **EMG** - Electromyography; **FAP** - Familial Amyloid Polyneuropathy; **FIM** - Functional Independence Measurements; **mBMI** - Modified Body Mass Index; **MRC S-S** - Medical Research Council Sum-Score; **NIS** - Neuropathy Impairment Score; **NYHA** - New York Heart Association; **PND** - Polyneuropathy Disability; **QoL** - Quality of Life; **SF-36/12** - ShortForm 36/12; **VAS** - Visual Analog Scale.

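### Pooled averages at reimbursement milestones mix starting values with on-treatment values, so for the scored endpoints they would not describe change on Onpattro

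*Protocol*

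**What the plan says.** The second primary objective (section 6.1) is "To determine the clinical impact of Onpattro® use in adult patients with hATTR, in real world circumstances", judged on neurological and cardiac symptoms. The secondary objective (section 6.2) asks the same for quality of life.

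Table 1 in section 9.2 is the only timepoint structure given for these outcomes. It has four columns: EAP treatment initiation, first reimbursement, reimbursement prolongation and last evaluation. Three footnotes decide who is in each column:

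- Footnote 1 limits the first column to EAP patients.
- Footnote 4, "For patients not included in the EAP", moves age, previous treatment and Onpattro start date to the first-reimbursement column for those patients.
- Footnote 2 widens the prolongation column to patients "or no longer treated/still on initial reimbursement".

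On analysis, section 11.3 says: "The analysis of the collected information will only consist of descriptive data such as frequencies, aggregated averages, standard deviations and ranges". It adds that no formal analysis plan exists, that missing values are not filled in, and that "Statistical analyses will only be performed on parameters collected in sufficient numbers".

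**The concern.** Clinical impact in a progressive disease means change within patients since they started treatment. The milestones in Table 1 are administrative and do not line up with treatment start. The same column holds a starting value for one patient and a value after more than a year of infusions for another. The first column holds only some of the patients, and the third mixes patients who were prolonged, who stopped, and who are still on their first reimbursement period.

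If the scores are averaged by milestone and the averages are read across the table, the apparent trend reflects three things at once: real change, differences between EAP and non-EAP patients, and unequal time on drug. Section 8.1 expects about 9 to 12 treated patients, so a few can move an average. The results go into a report to the Belgian Health Insurance Agency on reimbursement (section 5.2), which will naturally look for a treatment effect in them.

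**Working it through.** The protocol gives no figure of its own to reproduce here. The check is date arithmetic, followed by a range over the unknown EAP share.

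**Inputs from the protocol**

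- Earliest start: the EAP "was launched on 01 July 2018, to allow patients with hATTR to receive Onpattro" (section 5.1).
- Start of Belgian reimbursement: 01 December 2019 (section 5.1).
- Last evaluation: "up to 01 February 2021, if available" (Table 1, footnote 3).
- Sub-cohort size: about 9 to 12 (section 8.1).

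**Intervals**

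- EAP launch to reimbursement: 518 days, 17 months.
- Reimbursement to cut-off: 428 days, 14 months.
- EAP launch to cut-off: 518 + 428 = 946 days, 31 months.

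**Time on treatment in the first-reimbursement column.** Non-EAP patients contribute 0 months if this is their starting point. EAP patients contribute up to 17 if reimbursed on 01 December 2019. With k EAP patients among n, mean exposure is at most 17k/n. The share k is not in the protocol, so it is varied here as an assumption, with n = 12:

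| EAP patients (assumed) | First reimbursement: 17k/12 | Last evaluation: (31k + 14(12 − k))/12 | Difference | Difference as share of exposure since own start |
|---|---|---|---|---|
| 3 | 4.2 | 18.2 | 14 | 77% |
| 6 | 8.5 | 22.5 | 14 | 62% |
| 9 | 12.8 | 26.8 | 14 | 52% |

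For any mix of EAP and non-EAP patients, the first-reimbursement column is neither a baseline nor a fixed follow-up. Reading from it to last evaluation covers 14 months whatever the mix, although mean exposure since own treatment start is longer. The ambiguity disappears at the extremes. If nobody came from the EAP, the column is a baseline for all. If everybody did, it is an on-treatment visit for all.

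**Who is in the columns.** Reading from EAP initiation to first reimbursement compares different sets of patients. As an illustration only, assume 6 EAP patients with mean NIS 60, 6 non-EAP patients with mean NIS 40, and no change in anyone. The first column averages 60. The second averages (6 × 60 + 6 × 40)/12 = 50. The 10-point fall comes entirely from who is counted.

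**Which endpoints are affected.** Sections 11.1.1 and 11.1.2 list NIS, MRC, FIM, ACTIVLIM, CADT, VAS, PND, FAP, NYHA and the quality-of-life measures as scores or classes, with no change defined. EMG, ECG and echocardiography status are recorded as worsened, stable or improved. These are changes by construction, but the protocol does not say relative to which visit.

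**The case against.** The strongest reply is that this is a small, hypothesis-free chart review made for a reimbursement agreement, so reimbursement milestones suit its purpose. Section 11.3 does not say that averages are taken by milestone or compared, and its list of summaries is introduced as examples. Section 11.4 says that no groups will be compared. The sub-cohort data are individual (section 11.2), so a sensible analyst could compute paired changes.

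Part of this stands. The absence of testing and of a power calculation is no fault here, and milestone averaging is inferred. But Table 1 offers no other timepoints, and the protocol rules out leaning on a later plan by saying that there is none. That the data allow paired change makes the remedy cheap. It does not make it planned.

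Several stronger readings are tempting, and the protocol does not support them:

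- A reader might infer that no endpoint captures change. EMG, ECG and echocardiography do.
- A reader might infer that time on treatment cannot be recovered. Table 1 collects start, stop and interruption dates and cycle counts, which give approximate exposure. What it does not list is the date of each assessment.
- A reader might infer that every column is restricted to different patients. Only the first is, by design. Footnote 2 keeps stopped and still-initial patients in the third, so columns two to four target essentially the same people apart from missing data. The cost there is mixed treatment status.
- A reader might infer that the sufficient-numbers clause lets endpoints be dropped on their results. Its criterion is the amount of data. The fair complaint is that no threshold is set.

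**Conclusion.** The point holds for the scored endpoints. Followed as written, pooled summaries at the Table 1 milestones would not describe change on Onpattro, which the second primary objective needs. For EMG, ECG and echocardiography the gap is narrower: the reference visit is undefined.

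The firm part of the size is the spread in exposure: 0 to about 17 months at first reimbursement, and up to 14 or up to 31 months at last evaluation. It rests on non-EAP patients starting at first reimbursement, which footnote 4 implies but does not state, and on the national reimbursement date. An EAP patient reimbursed later could exceed 17 months, and one who entered the program after launch could have less.

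The bias in any score is unknown, because neither the EAP share nor the scores of the two groups are given. The 10-point NIS shift shows that an artefact is possible. It is not an estimate.

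Should-fix rather than must-fix: the survey is descriptive, and individual data and start dates are already collected.

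**What to change.** In section 11.3:

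1. Define each patient's baseline as the last assessment before the first infusion: EAP initiation for EAP patients, first reimbursement for the others. Use the same baseline as the reference for the worsened/stable/improved endpoints.
2. Make the main clinical summary the paired within-patient change, or shift for ordered categories, from that baseline. Give the number of pairs and the time on treatment.
3. Show EAP and non-EAP starters separately, and flag values from patients off treatment.
4. Replace the sufficient-numbers sentence with a commitment to report every listed endpoint with the number available over the number expected.

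In Table 1, add an assessment date to each evaluation, since start date and cycle counts place a score in time only approximately.

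The cost is one date field per evaluation and a rewritten paragraph. The drawback is that some timepoints will have fewer pairs than raw values.
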